#### Economic analysis

A within-trial cost-effectiveness analysis will be carried out, taking the NHS/personal social services perspective preferred by NICE [92]. Service use will be measured in interview using the AD-SUS [91], at baseline (covering the previous 3 months), at the 4 m, 9 m, and 24 m follow-up points, and at the four 3-monthly phone calls (covering the period since previous interview/phone call, thus ensuring coverage of the full 24-m period). Service use will be costed using nationally applicable unit costs (e.g. NHS Reference Costs for hospital contacts; Personal Social Services Research Unit (PSSRU) Unit Costs of Health and Social Care for community-based services; and the British National Formulary for medication). The TF-CBTp intervention will be directly costed taking a standard micro-costing approach [95]. Data on therapist time will be collected from clinical records (number and duration of face-to-face contacts) and unit costs will be based on the mid-point of the therapists’ salary, including all employer costs (National Insurance and superannuation) and appropriate overheads (capital, managerial, administrative, etc.). The cost of supervision will be included and indirect time (for, e.g. training, administration, meetings with other professionals) will be estimated using a questionnaire completed by each therapist on the time they spend on various direct and indirect patient-related activities.

The primary economic evaluation will be a cost-utility analysis carried out at the 9-m endpoint (end of therapy), in line with the clinical analyses, with outcomes expressed in terms of QALYs, calculated from the EQ-5D-5L [88], using the area under the curve approach [96]. Given evidence to suggest the EQ-5D may not be particularly sensitive in psychosis populations, the new ReQoL measure [89] and the primary clinical outcome measure (CAPS-5 [69]) will be included in secondary economic analyses. All three economic evaluations will be repeated at the 24-m follow-up to explore the longer-term impact of TF-CBTp compared to TAU.

Costs and QALYs will be compared at the 9-m and 24-m follow-up points and presented as mean values by trial arm with standard deviations. Mean differences in costs and 95% confidence intervals will be obtained by non-parametric bootstrap regressions to account for the non-normal distribution commonly found in economic data [97]. Cost-effectiveness will be assessed using the net benefit approach and following standard approaches [98]. A joint distribution of incremental mean costs and effects for the two groups will be generated using bootstrapping to explore the probability that TF-CBTp is the optimal choice compared to TAU, subject to a range of possible maximum values (ceiling ratio) that a decision-maker might be willing to pay for unit improvements in outcomes. Cost-effectiveness acceptability curves will be presented by plotting these probabilities for a range of possible values of the ceiling ratio [99]. These curves are a recommended decision-making approach to dealing with the uncertainty that exists around the estimates of expected costs and expected effects associated with the interventions under investigation and uncertainty regarding the maximum cost-effectiveness ratio that a decision-maker would consider acceptable. To provide more relevant treatment-effect estimates, all economic analyses will include adjustment for the variable(s) of interest and baseline covariates [100], which will be pre-specified and in line with the clinical analyses. The primary analysis will be a complete case analysis with the nature and impact of missing data, in particular those lost to follow-up, explored in sensitivity analyses.

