There has been some suggestions that remote delivery may adversely impact the therapeutic relationship, with some studies [46, 54] but not others [55] finding a slightly higher drop-out rate than in in-person PTSD treatments. To minimise this possibility, we incorporated the extensive guidelines that have been published for successful delivery of remote therapy in our therapy protocol and training [42, 56, 57]; see also resources at https://oxcadatresources.com/covid-19-resources/). In addition, our therapy protocol already includes digital materials (around providing psychoeducation and promoting control), which will benefit digital platforms and will facilitate therapy engagement.

We have included a measure of therapeutic alliance for participants in the therapy group that will allow us to monitor the potential impact of different modes of delivery on the therapeutic relationship. We will record the type of delivery used for each assessment and therapy session, which will enable us, if required, to do post hoc analyses comparing the use of different platforms on outcomes.

If appropriate, the adaptations will be deliverable for the entirety of the study, rather than just during the pandemic. Pre-pandemic, the drivers for developing remote treatments were to increase access to therapy when in-person meetings were not feasible [49]. Unsurprisingly, during 2020, there has been a step change in the implementation of these methods across the UK (and internationally). It is likely that some of these changes will remain post-pandemic, and we will be able to continue to offer remote delivery throughout the trial for those who prefer it. There is limited research evidence on patient preferences, but one study found that up to 50% of participants preferred remote delivery [46].

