#### Covid-19 adaptations to the protocol

In response to the global pandemic, the research team has made adaptations to the protocol to enable the trial to continue in the event of social distancing restrictions being in place. Recruitment, assessment, and therapy delivery will be conducted remotely, using videoconferencing or telephone, where it is not possible to see participants in-person. Study documents such as Participant Information Sheets and trial leaflets will be sent either by e-mail or post. Wherever possible, participant choice for mode of attendance will be respected, unless it conflicts with NHS trust and University guidance at any given time.

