### Strategies to improve adherence to interventions {11c}

The intervention will be delivered by trained psychological therapists with experience of working with severe mental health problems, to ensure competence in engaging this complex population. They will receive training in delivering TF-CBTp by the study team (3 days training, with 2-day booster sessions in subsequent years). Therapists will travel to participants’ team base or home/residence if required, or conduct sessions remotely, to maximise retention in the therapy.

Three related aspects of therapy fidelity will be monitored and assessed: (i) participants’ adherence to the therapy, (ii) therapist adherence to the manual, (iii) therapist competence in delivering the therapy.

Participants’ adherence to the therapy will be assessed by recording the number of sessions offered and attended, including length of sessions attended. Completion of between-session tasks (i.e. therapy ‘homeworks’) will also be monitored.

Study-specific therapist adherence and competency scales will be developed to fit the therapy manual. Adherence will consist of a checklist of therapeutic procedures and therapy milestones extracted from the manual, to record content of sessions in terms of agenda targets, homework tasks, and change strategies used in all phases of the manual. Competence in applying these procedures will be assessed by adapting items from existing measures to assess skills and competences related to basic CBT, psychosis work, and PTSD trauma-focused work (PTSD-adapted version of the Cognitive Therapy Scale – Revised (CTS-R) [73], available at oxcadatresources.com).

To monitor therapy adherence, therapists will complete the adherence checklist following each session. These data will be extracted at regular time points throughout the trial to check therapy milestones are being met and ensure the therapy protocol is being followed. This ongoing monitoring will pick up on any adherence issues across sites or individual therapists and will inform training and supervision content.

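### TF-CBTp contact time is to be costed from face-to-face contacts, although therapy may also be given by video or telephone; applied as written, remote session time would go uncosted

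*Protocol article*

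**What the plan says.** All references are to the protocol article.

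- **Economic analysis.** The method is stated as "The TF-CBTp intervention will be directly costed taking a standard micro-costing approach". For contact time: "Data on therapist time will be collected from clinical records (number and duration of face-to-face contacts". The section then adds other therapist inputs: "The cost of supervision will be included and indirect time (for, e.g. training, administration, meetings with other professionals) will be estimated using a questionnaire". Each therapist completes that questionnaire, which asks "on the time they spend on various direct and indirect patient-related activities".
- **Covid-19 adaptations to the protocol.** "Recruitment, assessment, and therapy delivery will be conducted remotely, using videoconferencing or telephone, where it is not possible to see participants in-person".
- **Covid-19 adaptations to the trial.** The remote option is not confined to the pandemic: "we will be able to continue to offer remote delivery throughout the trial for those who prefer it". This section also says that some telephone sessions are usual in clinical practice with this population, that the mode of each therapy session will be recorded, and that in-person therapy stays available to those who choose it.
- **Strategies to improve adherence to interventions {11c}.** Therapists may hold sessions remotely. Participants' adherence is assessed by "recording the number of sessions offered and attended, including length of sessions attended", with no restriction by mode.

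**The concern.** A micro-costing is only as complete as its count of resource use. Here the count of therapist contact time is tied to a term that, in ordinary use, excludes a telephone call and may exclude a video call. The protocol nonetheless treats both as accepted ways of delivering the therapy.

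A remote session takes up therapist time as an in-person session does. If remote sessions are not counted, the loss falls entirely on the TF-CBTp arm, because TAU has no micro-costed therapy. The error therefore has one direction: lower incremental cost and a higher apparent probability that TF-CBTp is cost-effective. It would enter the primary cost-utility analysis at 9 months, the secondary economic analyses using ReQoL and CAPS-5, and the repeats at 24 months. The bootstrap and the acceptability curves would not reveal it, since they describe sampling uncertainty and take the cost of each participant as given.

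**Working it through.** The protocol states no intervention cost and no expected remote share, so there is no figure of its own to reproduce. The check has two parts.

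**1. Does anything else in the plan capture remote contact time?**

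- *Indirect time.* The examples given are training, administration and meetings with other professionals. A therapy session by telephone is none of these.
- *The therapist questionnaire.* It asks about direct as well as indirect activities, but its stated use is to estimate indirect time. It is completed per therapist, so it is not a record of each participant's remote sessions.
- *The service-use interview (AD-SUS).* The protocol costs the trial therapy separately. It also has the follow-up interviews done by workers blind to allocation, so this is not an evident route for counting trial sessions.
- *The session records.* Number, length and mode of sessions are all to be recorded, but for adherence and for possible comparisons of delivery mode. The costing sentence does not draw on them.

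No other stated source clearly fills the gap.

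**2. How much contact time is at stake under the literal reading?**

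Inputs from Intervention description {11a}: about 26 sessions of 60 to 90 minutes in the first 6 months, then 3 monthly sessions. No length is given for the last three; 60 to 90 minutes is assumed. Full attendance is assumed, as is the same average length for remote and in-person sessions.

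- Planned sessions: 26 + 3 = 29.
- Planned contact hours per participant: 29 × 1.0 = 29.0 h to 29 × 1.5 = 43.5 h.
- Hours omitted = planned hours × r, where r is the share of sessions not counted as face-to-face.

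| Assumed r | Hours omitted per participant | Share of contact time still costed |
|---|---|---|
| 0% | 0 | 100% |
| 10% | 2.9 to 4.35 | 90% |
| 30% | 8.7 to 13.05 | 70% |
| 50% | 14.5 to 21.75 | 50% |
| 70% | 20.3 to 30.45 | 30% |

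The values of r are assumptions. The protocol cites one study in which as many as half preferred remote delivery, and a waiting list at one trial site where 30% declined it. Neither is a forecast of the share of trial sessions. If video is accepted as face-to-face, r is the telephone share alone.

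The table concerns contact time, not total intervention cost. Supervision and indirect time are costed as well. The protocol does not say whether indirect time will be scaled to contact time; if it is, the omission carries over to it.

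**The case against.** The strongest reply concerns the word itself. The costing sentence is the only place where the article uses face-to-face. When it contrasts modes of delivery it says in-person. Within the costing text the contrast is with indirect time, so the term may simply mean direct client contact in any mode. The questionnaire does ask about direct activities, and every record needed for a full costing is already planned. On that reading nothing is lost.

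Part of this stands. The term is undefined, the broader reading is possible for video, and no data are irrecoverable. But the reading is strained for telephone, which the protocol names as a delivery mode. A rule that two analysts could apply differently, with different intervention costs, is badly fixed.

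Three stronger readings are tempting and are not supported:

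- *That therapy is delivered remotely throughout.* Remote delivery is an option available throughout, alongside in-person therapy.
- *That missed appointments are wrongly left out of the cost.* The protocol does not say that they will be excluded, and a condensed article may leave such detail to the full plan.
- *That the sentence was overlooked when remote delivery was added.* The article gives no drafting history for it.

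**Conclusion.** The point holds as an inconsistency between the costing rule and the permitted delivery of the therapy. Followed literally, the rule omits remote therapist time in the TF-CBTp arm only and understates contact time by the remote share. The protocol itself expects at least some telephone sessions, so on that reading the share is unlikely to be zero. Its size is unknown, and the hours above are illustrative.

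A reader might infer that the intervention cost will certainly be understated, or might put a monetary or QALY value on the loss. The documents support neither. The first depends on the literal reading of an undefined term. The second needs a remote share, an hourly cost and a threshold that the protocol does not give. The clinical primary analysis is unaffected.

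**What to change.** In the Economic analysis section, replace the reference to face-to-face contacts with: number and duration of all therapy contacts (in-person, video and telephone). Name as the source the session records already planned, which hold the mode of each session and the number and length of sessions attended.

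This costs one phrase and no new data collection. The price is an intervention cost that may be somewhat higher, and so less favourable to TF-CBTp, than under the literal rule.

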**Methods:**

Rater-blind, parallel arm, pragmatic randomised controlled trial comparing TF-CBTp + treatment as usual (TAU) to TAU only. Adults (*N* = 300) with distressing post-traumatic stress and psychosis symptoms from five mental health Trusts (60 per site) will be randomised to the two groups. Therapy will be manualised, lasting 9 months (m) with trained therapists. We will assess PTSD symptom severity (primary outcome); percentage who show loss of PTSD diagnosis and clinically significant change; psychosis symptoms; emotional well-being; substance use; suicidal ideation; psychological recovery; social functioning; health-related quality of life; service use, a total of four times: before randomisation; 4 m (mid-therapy); 9 m (end of therapy; primary end point); 24 m (15 m after end of therapy) post-randomisation. Four 3-monthly phone calls will be made between 9 m and 24 m assessment points, to collect service use over the previous 3 months. Therapy acceptability will be assessed through qualitative interviews with participants (*N* = 35) and therapists (*N* = 5–10). An internal pilot will ensure integrity of trial recruitment and outcome data, as well as therapy protocol safety and adherence. Data will be analysed following intention-to-treat principles using generalised linear mixed models and reported according to Consolidated Standards of Reporting Trials-Social and Psychological Interventions Statement.

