In relation to cost-effectiveness, we will collect data on service use and health-related quality of life at all assessment time points. In addition, service use will be assessed for the previous 3 months at the ‘keeping in touch’ phone calls between the end of therapy (9 m post-randomisation) and final follow-up (24 m post-randomisation), to maximise the accuracy of these data. See ‘Economic analysis’ section for further details.

Acceptability of the therapy, through qualitative interviews, will also be assessed as a secondary outcome in the therapy group, and in therapists delivering the therapy. This qualitative element will identify key aspects of acceptability and tolerability in receiving and implementing the therapy that could not be detected by quantitative measures alone. Therapeutic alliance will also be assessed in the intervention group only (Fig. 3).

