## Statistical methods

### Statistical methods for primary and secondary outcomes {20a}

#### Primary and secondary outcomes

We will report data in line with the CONSORT-SPI [74] statement showing attrition rates and loss to follow-up. All analyses will be carried out using the intention to treat principle, incorporating data from all participants including those who do not complete therapy. Every effort will be made to follow up all participants in both arms for research assessments.

Analyses will be conducted in Stata version 15 or later. Descriptive statistics within each randomised group will be presented for baseline values. These will include counts and percentages for binary and categorical variables, and means and standard deviations, or medians with lower and upper quartiles, for continuous variables, along with minimum and maximum values and counts of missing values. There will be no tests of statistical significance or confidence intervals for differences between randomised groups on any baseline variable.

Treatment effects on primary and secondary outcomes will be estimated using linear mixed models. Fixed effects will be centre, baseline assessment for the outcome under investigation, group, time (categorical), and time × group interactions. Participant and therapist will be included as random intercepts. Marginal treatment effects will be estimated and reported for each time point as adjusted mean differences in scores between the groups with 95% confidence intervals and 2-sided *p*-values. For binary secondary outcomes, the same approach will be followed using logistic mixed models and effects will be reported as conditional odds ratios.

The analysis will be conducted in two separate stages. The primary analysis will estimate treatment effects at the primary endpoint of 9 m, using all outcome data from 4 and 9 months. Analysis will take place after the last participant has completed their 9 m assessment and will report the estimated effects at 4 and 9 months. The results will not be shared with the blinded assessors, nor outside of the STAR team, until all 24-m assessments have been completed, to avoid any biases on data collection.

The secondary analysis will estimate treatment effects at 24 m, using all outcomes from 4, 9, and 24 months. Analysis will take place after the last participant has completed their 24-m assessment, and will report the estimated effect at 24 m.

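### The economic base case is a complete-case analysis, although the clinical analysis keeps partly observed participants under missing at random

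*Protocol article*

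**What the plan says.** The Economic analysis section plans a cost-utility analysis at 9 months, with QALYs from the EQ-5D-5L by area under the curve and costs from the AD-SUS, repeated at 24 months. On missing data it says "The primary analysis will be a complete case analysis with the nature and impact of missing data" left to sensitivity analyses, above all for people who drop out. It does not name the sensitivity methods. It also says that "all economic analyses will include adjustment for the variable(s) of interest and baseline covariates", in line with the clinical analyses.

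The clinical analysis is set up differently. Under Primary and secondary outcomes: "All analyses will be carried out using the intention to treat principle, incorporating data from all participants including those who do not complete therapy". The abstract says: "Data will be analysed following intention-to-treat principles using generalised linear mixed models". Section {20c} specifies maximum likelihood under missing at random. Section {18b} explains that the 4-month visit gives the mixed model data on people who have dropped out by the primary endpoint.

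On recall, Outcomes {12} says of the phone calls: "In addition, service use will be assessed for the previous 3 months", and the abstract agrees. The Economic analysis section describes the calls as "covering the period since previous interview/phone call, thus ensuring coverage of the full 24-m period".

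**The concern.** A 9-month QALY needs utilities at baseline, 4 and 9 months, and a 9-month cost needs service use over the whole period. A complete-case rule drops anyone with a gap in either, including someone with full 4-month data who misses the 9-month visit. The clinical model retains that person.

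Two things are at stake. The first is comparability: Objectives {7} asks in one question whether the therapy is clinically and cost-effective, and the two answers would come from different participants. The second is validity: complete case with baseline adjustment is unbiased only if, given arm and those baseline covariates, completeness is unrelated to cost and utility. The incremental cost, the QALY difference and the acceptability curve all depend on that condition.

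**Working it through.** **Inputs.** From Sample size {14}: 300 randomised, 20% attrition to 9 months, 120 per group analysed. Not given in the document, so assumed: 85-95% of those seen at 9 months also have complete 4-month EQ-5D-5L and AD-SUS; people with missing data differ from those observed by 0.25-0.5 SD.

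**1. The plan's own figure.** 300 × (1 − 0.20) = 240 = 2 × 120. This reproduces. It is an allowance for the primary clinical endpoint. No figure is given for economic data or for 24 months.

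**2. Exclusions from attrition alone.** 300 − 240 = 60, or 20%.

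**3. Precision.** Standard error relative to complete data on all 300: √(300/240) = 1.12. This is a ceiling on what any method could recover, because imputation restores only part of the lost information.

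**4. Incomplete 4-month data.** The EQ-5D-5L asks about health on the day, so a missed 4-month value cannot be collected later.
- 95% complete: 240 × 0.95 = 228; 72 excluded (24%); √(300/228) = 1.15.
- 85% complete: 240 × 0.85 = 204; 96 excluded (32%); √(300/204) = 1.21.

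**5. Mismatch with the clinical analysis.** On the same assumption, 240 − 228 = 12 to 240 − 204 = 36 people seen at 9 months could be in the clinical model but not in the economic base case. To these add those of the 60 lost at 9 months who attended at 4 months. The document does not say how many that would be.

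**6. Bias.** The shift in one arm's mean is the missing share times the gap between missing and observed: 0.20 × 0.25 = 0.05 SD to 0.20 × 0.5 = 0.10 SD. It cancels in the comparison if share and gap are equal in both arms. The protocol gives reason not to take that for granted. The missing-data paragraph under Primary and secondary outcomes plans to test whether adherence is associated with missing data. Section {20c} allows weighting for non-adherence and other intermediate outcomes as predictors of later loss. Section {18b} sees long gaps without contact as a particular concern for controls and for people who end therapy early. Adherence and intermediate outcomes arise after randomisation, so baseline covariates cannot stand in for them, whereas imputation or weighting can use them.

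**7. Recall.** Calls are due at 12, 15, 18 and 21 months, so on schedule both descriptions cover the same 3 months. They part when a contact is missed or moved. If the 15-month call is missed, a fixed 3-month window at 18 months covers 15-18 and loses 12-15; recall since the last contact covers 12-18. If the 9-month visit takes place at 8 months, as the ±1-month window allows, a fixed window at 12 months covers 9-12 and loses one month.

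**The case against.** The strongest defence is that the plan already softens the problem. It adjusts for baseline covariates and promises missing-data sensitivity analyses, whose methods a condensed article may leave to the analysis plan. Complete case with that adjustment is valid if missingness depends only on the adjusted covariates. Retention measures are good: the economic measures come straight after the CAPS-5 and PSYRATS, and remote and home visits are offered. All of this stands, but the sensitivity analyses do not change which estimate is the headline.

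A reader might infer several stronger points that the document does not support.
- **That the excluded share is known to be non-random.** No section says so, and the association with adherence is left to be tested. That people in crisis are the ones who miss contacts is plausible, but it is not in the protocol.
- **That complete case flatly contradicts intention to treat.** The sentence on all analyses sits under the clinical outcomes, and its explanatory clause concerns therapy completion. Complete cases can be analysed as randomised. The clinical model does not use all 300 either, since someone with no follow-up contributes nothing to it. What remains is a tension with the wording about all participants.
- **That the 24-month analysis would collapse.** Multiplying 80% retention by 85-95% completeness at six earlier contacts gives 300 × 0.80 × 0.85⁶ = 91 to 300 × 0.80 × 0.95⁶ = 176. This borrows the 9-month allowance, treats misses as independent although they tend to cluster in the same people, and treats missed calls as unrecoverable, against the recall rule in the Economic analysis section.

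**Conclusion.** The point holds as a cheap and worthwhile improvement to a choice that the protocol states outright. The base case discards at least about 60 of 300 at 9 months if attrition is as planned, and 72-96 if 4-month completeness is 85-95%, which is an assumption. The result is less precise than it need be, is at risk of bias of unknown size and direction, and is not in line with the clinical analysis that it is meant to match. How much bias arises depends on missingness that has yet to be observed.

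The sample size and the primary clinical analysis are unaffected. Cost-effectiveness appears in the research question but is listed among the secondary aims, which limits the weight of the point. The recall difference is a minor matter of wording that has consequences only after a missed or shifted contact.

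**What to change.** 1. Make a missing-at-random method the base case at 9 and 24 months. One suitable choice is multiple imputation by arm, with the analysis covariates, observed 4-month and other follow-up costs and utilities, clinical outcomes and, in the therapy arm, sessions attended in the imputation model, combined with the planned bootstrap. Inverse probability weighting, which the protocol already names for the clinical analysis, is an alternative.
2. Keep the complete-case analysis as a sensitivity analysis.
3. Say whether the intention-to-treat sentence covers the economic evaluation.
4. Reconcile the abstract and Outcomes {12} with the Economic analysis section in favour of recall since the last completed contact, and record the period that each contact covered.

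The cost is a change of wording plus modest analyst and computing time. The analysis change needs no new data. The recall rule lengthens recall after a missed call, at some loss of accuracy, but avoids an outright gap in costs. The analysis change should be settled before the economic data are examined by arm.
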